**2.4. Genetics Sub-study**

Genes significantly influence vitamin D status (29-43%) and polymorphisms in vitamin D pathway genes (especially the vitamin D receptor (VDR) gene) have been associated with a variety of diseases^86^, including respiratory tract infections^87^. Although most studies to date have examined only a few *VDR* polymorphisms, more are beginning to comprehensively investigate polymorphisms in the *VDR* as well as in other vitamin D pathway genes, such as the vitamin D–binding protein gene (*GC*), 7-dehydrocholesterol reductase (*DHCR7*), *CYP27B1* and *CYP24A1*. These genes encode enzymes that, respectively, synthesize and degrade 1α,25-(OH)_2_-vitamin D and are the genes that have been most strongly linked to circulating 25OHD levels^88,89^. There is limited evidence suggesting that individuals carrying risk alleles for lower 25OHD concentrations have an enhanced response to supplementation^90^, but this area is largely unexplored.

Although genetic analysis is outside the scope of this study, we will collect an additional tube of blood at baseline from consenting participants, which will be stored for future genetic analysis to determine the impact of genetic factors on the response to supplementation.

**3. RESEARCH DESIGN AND METHODS**

**3.1. Hypothesis**

The main hypothesis of this project is that providing vitamin D as an adjunct to standard antibiotic therapy will accelerate the resolution of pulmonary inflammatory infiltrate in CAP.

The specific objectives are to determine whether providing a single, oral, high-dose bolus of vitamin D in adults hospitalised with CAP will:

1. Improve the resolution of pulmonary inflammatory infiltrate compared with placebo.

2. Improve patient outcomes compared with placebo.

**3.2. Study Overview**

The study is a randomised, double blind, placebo-controlled trial in adults admitted to hospital with a confirmed radiological diagnosis of CAP. Participants will be randomised to receive a single oral dose of 200,000 IU vitamin D_3_ or matching placebo within 48 hours of admission to hospital. The primary outcome measure will be the resolution of pulmonary inflammatory infiltrate on chest x-ray at 6 weeks (± 1 week) after receiving study treatment. Secondary outcomes will include measures of patient outcomes including; length of hospital stay, in hospital mortality, intensive care admission rates, rates of relapse and readmission to hospital after discharge, 6 week post-study treatment mortality rates, 12-month mortality rates and the resolution of symptoms and return to normal activity at 6 weeks post-study treatment as assessed from hospital records and a structured telephone interview.

**3.3. Participants**

Participants will be recruited from CAP patients admitted to Christchurch Hospital and Princess Margret Hospital sites. On average, 400 to 500 people are admitted to these hospitals annually with a diagnosis of CAP, with the peak incidence occurring over the winter months (June to August).

Inclusion criteria:

1. A confirmed radiological diagnosis of pneumonia, defined as:

‘New inflammatory infiltrate on a chest radiograph where patients have an acute illness with clinical features of pneumonia and radiographic pulmonary shadowing that is at least segmental or present in one lobe and is neither pre-existing or because of some other known cause.’

1. <48 hours since admission to hospital
2. Age ≥ 18 years
3. Ability to give informed consent
4. Ability to orally consume the study medication
5. Ability to attend a follow-up appointment at 6 weeks post-study treatment for a chest x-ray

Exclusion criteria:

1. Pneumonia is not the principal reason for admission
2. Pneumonia associated with bronchial obstruction, bronchiectasis, or known tuberculosis
3. Use of vitamin D_3_ supplements other than as part of a multivitamin preparation where the daily intake would not exceed 400 IU.
4. High plasma corrected calcium > 2.6 mmol/L (corrected for plasma albumin concentration)
5. Use of immunosuppressants (e.g. doses of prednisone >10mg, methotrexate, azathioprine and cyclosporin)
6. Any prior history of hypercalcaemia, nephrolithiasis or sarcoidosis
7. Current kidney disorders requiring dialysis treatment or polycystic kidney disease
8. Cirrhosis of the liver
9. Women who are pregnant or are breastfeeding*
10. Already enrolled or planning to enrol in a research study that would conflict with full participation in the study or confound the observation or interpretation of the study findings (e.g. where vitamin D levels are tested and results are known by the participant; where the participant is required to take conflicting medications)

* At the 6 week follow-up women of reproductive age that think/know they are pregnant will also be excluded from taking further part in the study.

**3.4. Intervention**

Participants randomised to the active treatment will receive a single oral dose of 200,000 IU vitamin D_3_ < 48 hours of admission to hospital with a confirmed radiological diagnosis of CAP. Those randomised to placebo will receive matching inactive tablets that will be administered in an identical regimen. The vitamin D_3_ and matching placebo tablets will be sourced from Tishcon Corp (an accredited pharmaceutical company in New Jersey, USA). All treatments will be directly administered to participants by research staff upon enrolment into the study.

The dose of 200,000 IU vitamin D was chosen to rapidly increase serum 25OHD levels to approximately 80-100 nmol/L and is based on data from two studies that have assessed the pharmacokinetics and safety of high dose vitamin D_3_. One study in healthy adults showed that a single oral dose of 100,000 IU vitamin D_3_ increased plasma 25OHD levels from around 65 nmol/L to ≥ 80 nmol/L within 24 hours and reached a maximum of approximately 100 nmol/L at 7 days following consumption^39^. A second study in elderly women showed that a single oral dose of 300,000 IU sharply increased 25OHD levels from approximately 30 nmol/L to 125 nmol/L after 3 days and levels reached a maximum of approximately 150 nmol/L within 30 days of consumption before decreasing^38^. There were no safety issues or incidences of hypercalcaemia reported for either study. Similarly, two further studies that used single large bolus doses of 500,000 IU vitamin D showed that 25OHD levels were between 150-210 nmol/L one month following supplementation and neither study reported any incidences of hypercalcaemia^91,92^. Thus, large single doses of vitamin D_3_ up to 500,000 IU have been shown to be safe and effective for rapidly raising 25OHD levels above 80 nmol/L.

**3.5. Study Period**

The study will be conducted from June 2013 to December 2014 or until the sample size has been reached. Recruitment will be conducted as potential participants are admitted to hospital, identified and enrolled. Participants will be enrolled and receive their study treatment < 48 hours of admission to hospital. All participants will be observed from the time of the study treatment being given until 6 weeks (± 1 week) after receiving study treatment. This observation period was chosen as generally, 6 weeks is the standard clinical time point utilised for patients that have had pneumonia to assess its resolution by chest x-ray.

**3.6. Data Collection**

**3.6.1. Chest X-Ray**

The main outcome measure will be the resolution of pulmonary inflammatory infiltrate. Participants will be asked to undergo a follow-up chest x-ray, 6 weeks (± 1 week) after receiving study treatment.

**3.6.2. Blood Tests**

Blood samples will be collected at recruitment and at 6 weeks (± 1 week) after receiving study treatment and will be stored. Vitamin D (25OHD) levels will be measured on baseline blood samples at the end of the 6 week follow-up period to assess the proportion of people recruited into the study with deficient levels (<25 nmol/L). These baseline measures will be fed-back to the participant’s GP who will be responsible for the on-going care of the participant. The final blood sample collected at the end of the 6 week post- study treatment follow-up period will be stored and 25OHD levels measured after all participants have completed the 6 week follow-up period so as not to compromise the blinding of participants or research personnel. Plasma calcium and albumin levels will be measured in real-time on all samples collected and the corrected plasma calcium (i.e. corrected for plasma albumin concentration, as is standard laboratory practice) will be reported in order to check for hypercalcaemia (an elevated plasma corrected calcium is > 2.6 mmol/L). Only the corrected plasma calcium levels will be made available to investigators before the end of the 6 week follow-up period.

**3.6.3. Assessment of Patient Outcomes**

Clinical data including basic demographics, routine haematological and biochemical information, length of hospital stay, in-hospital mortality, intensive care admission rates, amount and duration of antimicrobial therapy and rates of relapse and readmission to hospital and mortality rates at 6 weeks post-study treatment will be obtained from patient hospital records. For all participants, a CURB65 pneumonia severity score will be calculated from the clinical data collected. Research staff will also conduct a telephone interview with study participants at 6 weeks post-study treatment to complete a questionnaire regarding the resolution of symptoms and if the participants have returned to normal activity. Twelve-month mortality rates will be obtained from national databases.

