**3.7.4. Follow-up**

At 6 weeks (± 1 week) post-study treatment all participants will be required to undergo a chest x-ray and provide a further blood sample for plasma calcium and serum 25OHD measures. Any women of reproductive age who thinks/knows they have become pregnant within the 6-week follow-up period will be excluded from further participation in the study and will not have a chest x-ray at 6 weeks. All participants will also be contacted by research staff at 6 weeks post-study treatment to answer a questionnaire regarding the resolution of symptoms and the return to normal activity.

Clinical data including length of hospital stay, in-hospital mortality rates, mortality rates at 6 weeks post-study treatment, intensive care admission rates, amount and duration of antimicrobial therapy and rates of relapse and readmission to hospital will be obtained from patient hospital records at 6 weeks post-study treatment. Twelve-month mortality rates will be obtained from national databases. This data will be analysed and reported subsequently to that of the 6 week follow-up data so the analysis and publication of the primary study findings is not delayed.

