Disability is defined as a substantial disruption in a person’s ability to conduct normal life functions.

The relationship of the AE to Study Medication will be specified as follows:

1. Not related. In the investigators opinion, there is not a causal relationship between study medication and the AE.
2. Unlikely. Study medication is not likely to have any reasonable association with the AE.
3. Possibly. The AE could have been produced by the participant’s clinical state or study medication.
4. Probably. The AE follows a reasonable temporal sequence from the time of study medication administration and cannot be reasonably explained by the known characteristics of the clinical state.
5. Definitely. The AE follows a reasonable temporal sequence from the time of study medication administration.

AEs will be collected from the time of study drug administration through the follow-up period at 6 weeks post-study treatment. The investigators should attempt, if possible, to establish a diagnosis based on the presenting signs and symptoms. In such cases the diagnosis should be documented as the AE and not the individual sign/symptom. If a clear diagnosis cannot be established, each sign and symptom must be recorded individually.

The investigators should attempt to follow all unresolved AEs and/or SAEs observed during the study until they are resolved or judged medically stable, or are otherwise medically explained. If there is any doubt about whether the information constitutes a SAE, the information is treated as a SAE.

Certain information, although not considered an SAE, must also be recorded, reported, and followed up as indicated for an SAE. This includes:

- Overdose of an investigational product as specified in this protocol with or without an AE.
- Inadvertent or accidental exposure with or without an AE.

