**5.2. Statistical Analysis**

All randomised participants will be included in the primary analysis. Data will be analysed on an intention to treat basis with dropout events reported on and examined for differential compliance between treatment and placebo arms. Primary analysis will be logistic regression of clear chest X-ray on treatment arm with covariates for age (grouped) and gender and if appropriate severity and comorbidities. Additional analyses will include covariates for initial 25OHD level and 25OHD level during the study and stratified analyses by 25OHD level at baseline; deficient (<25nm/l) and insufficient (<50nm/L). All data will be analysed in R (Vienna, Austria) or SAS (NC,USA).

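### Six-week mortality is drawn from hospital records only, so deaths after discharge may be missed although national death data are already planned for 12 months

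*Protocol*

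**What the plan says.** Two sections of the protocol fix the source of six-week mortality. Section 3.6.3 says "mortality rates at 6 weeks post-study treatment will be obtained from patient hospital records". Section 3.7.4 lists six-week mortality among the clinical data that "will be obtained from patient hospital records at 6 weeks post-study treatment".

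For the later time point the source changes: "Twelve-month mortality rates will be obtained from national databases" (section 3.6.3, repeated in 3.7.4). Section 3.7.4 adds: "This data will be analysed and reported subsequently to that of the 6 week follow-up data". The stated reason is to avoid delaying the main publication. The database query is therefore not planned to inform the six-week result.

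Section 3.2 gives a different account. After listing the secondary outcomes, including both six-week and 12-month mortality, it ends with "as assessed from hospital records and a structured telephone interview". That phrase may cover the whole list or only the last items (symptoms and return to normal activity). On the first reading it conflicts with sections 3.6.3 and 3.7.4 for mortality at both time points.

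Other provisions could bring a death to light. Section 3.7.4 says "All participants will also be contacted by research staff at 6 weeks post-study treatment". Section 4.3 makes death a criterion for a serious adverse event and says "AEs will be collected from the time of study drug administration through the follow-up period at 6 weeks post-study treatment".

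**The concern.** In-hospital mortality is already its own secondary endpoint. Six-week mortality differs from it mainly by adding deaths after discharge, yet both endpoints come from the same source. The protocol does not say whether the hospital records receive notice of deaths at home or in care. Its own switch to national databases at 12 months suggests that local records are not relied on for complete vital status.

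Two things are at stake. The first is the completeness of a named secondary endpoint with few expected events. The second is the classification of participants without a week-6 film. Section 5.2 says "All randomised participants will be included in the primary analysis" and has dropout reported and compared between arms. Death and failure to return mean different things for radiographic resolution, and telling them apart requires known vital status.

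**Working it through.** **Comparison of sources.** The protocol states no expected number of six-week deaths and no share of deaths outside hospital, so it has no figure to reproduce. The check is first a comparison of sections.

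- In-hospital mortality: hospital records (3.6.3, 3.7.4).
- Six-week mortality: hospital records (3.6.3, 3.7.4); possibly also telephone interview (3.2).
- 12-month mortality: national databases (3.6.3, 3.7.4); on one reading, hospital records and telephone interview (3.2).
- Six-week telephone call: section 3.6.3 directs it to participants and to symptoms and normal activity. No proxy contact or vital-status question is stated.
- Adverse events: section 4.1 covers those observed or volunteered, from dosing to six weeks, so detection depends on someone reporting.
- Withdrawal: section 3.7.9 lists loss to follow-up as a reason and states no check of vital status.

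The remaining gap is a participant who dies outside hospital, cannot be reached at six weeks, and for whom nobody reports the death. No section says how such a participant is classified.

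**Scale.** Inputs: 360 participants, up to 400 (3.7.1, 5.1); mortality of 6.5-8% in adults with community acquired pneumonia in New Zealand (2.1.2, no time horizon given); 80% retention (5.1).

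Expected deaths = N × mortality rate:

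- N = 360: 360 × 0.065 = 23.4; 360 × 0.08 = 28.8.
- N = 400: 400 × 0.065 = 26; 400 × 0.08 = 32.

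Let f be the share of deaths that no planned route records. The documents do not give f, so the values below are assumptions. Unrecorded deaths = N × rate × f, for N = 360:

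| f (assumed) | at 6.5% | at 8% | recorded rate if the true rate is 8% |
|---|---|---|---|
| 10% | 2.3 | 2.9 | 0.08 × 0.9 = 7.2% |
| 20% | 4.7 | 5.8 | 0.08 × 0.8 = 6.4% |
| 30% | 7.0 | 8.6 | 0.08 × 0.7 = 5.6% |
| 50% | 11.7 | 14.4 | 0.08 × 0.5 = 4.0% |

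Planned non-retention is 360 × 0.20 = 72, or 400 × 0.20 = 80. Whether that 20% is meant to include deaths is not stated. A few unrecorded deaths could sit in a group of that size without being noticed.

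**The case against.** The strongest reply is that the protocol does not depend on hospital records alone to learn of a death. Staff contact every participant at six weeks, and a film and blood sample are required then. Death is a serious adverse event within the collection window, investigators must follow up the outcome of each adverse event (4.1), and the monitoring committee is told within 24 hours of awareness (4.4). A reader might infer that deaths outside hospital will be missed or counted as lost, or that vital status is known only where hospital records hold it. The documents do not support either statement. What stands is that these routes are weakest for someone who cannot be reached, and that sections 3.6.3 and 3.7.4 do not name them as sources for mortality.

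The scale is also uncertain. Applying the 11% mortality seen below 25 nmol/L (2.3.3) to everyone gives 360 × 0.11 = 39.6 deaths, but section 3.7.1 aims for only about 120 deficient participants. With 4% for the remainder, 120 × 0.11 + 240 × 0.04 = 22.8, and even this applies the rate for levels above 50 nmol/L to the 25-50 group, whose mortality is not given. Section 3.3 requires participants to be able to consent, swallow tablets and attend at six weeks, which may select patients at lower risk.

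A reader might also infer a biased treatment comparison. Allocation is blinded and both arms use the same source, so nothing in the documents shows that missed deaths would differ by arm.

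For the primary endpoint, a participant who dies has no week-6 film whatever the data source. The handling of missing films may be set out in an analysis plan that is not shown, and section 3.7.9 already requires the reason for withdrawal to be recorded. The link is therefore limited to classifying missing films correctly. Finally, if the 12-month extract carries dates of death, it could correct the six-week figure, but only after the first report.

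**Conclusion.** The point holds as a risk and a worthwhile improvement; it is not a demonstrated error. The named source for six-week mortality may not record deaths after discharge and outside hospital, and section 3.2 does not clearly agree with sections 3.6.3 and 3.7.4. The six-week rate may be understated, and some missing week-6 films may be attributed to loss to follow-up when the participant had died.

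The number affected cannot be derived from the protocol. About 23-29 deaths in 360 participants follows from a background mortality with no stated time horizon, and the share that would go unrecorded is unknown. With so few events, even a few unrecorded deaths would matter for the absolute rate. The documents do not support a claim of between-arm bias or of distortion in the primary analysis method. If the hospital records already receive notice of all deaths, one sentence saying so would largely settle the matter.

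**What to change.** In sections 3.6.3 and 3.7.4, use date of death from the national databases to establish or confirm six-week vital status for all randomised participants. Keep hospital records, the telephone contact and serious adverse event reports as cross-checks. Use the result to classify each missing week-6 film as death or loss to follow-up, alongside any other recorded reason. Reword section 3.2 so that its sources for six-week and 12-month mortality match the other two sections.

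The cost is a wording change and one extract, from a source the trial already plans to query, taken once the last participant has completed week 6. The downside is a possible wait for database updates, whose length the documents do not indicate. If that would delay the primary report, check at least the participants with unknown vital status before database lock, and confirm six-week mortality from the 12-month extract.

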**3.7. Study Procedures**

**3.7.1. Recruitment of Participants**

All patients with a clincial diagnosis of pneumonia on admission to Christchurch Hospital are notified to a centralised patient registry which will be reviewed twice daily by members of the research team to identify potential participants. For these patients, computer records in the Depatment of Radiology will be selected electronically using an algorithm utilising key words such as pneumonia, consolidation and inflammatory infiltrate and the radiographs will be reviewed by a consultant radiologist to confirm the radiological findings. New admissions for CAP will be identified by study personnel on a daily basis on weekdays (Monday-Friday). Once identified, patients will be approached and asked to participate in the study within 48 hours of admission.

The study population will be comprised of at least the first 360 CAP patients that provide informed consent to participate (n= 180 per arm). However, to increase the possibility of seeing an effect, we aim to have ≈ 30% (n = 120) of the study cohort to be participants who are vitamin D deficient at baseline (25OHD levels <25 nmol/L). Thus, recruitment may need to continue to get the required numbers of deficient patients or until a maximum of 400 participants have been enrolled.

**3.7.2. Baseline Visit**

The study will be explained to potential participants by trained research staff. After informed consent has been obtained and eligibility has been assessed, all participants will be provisionally enrolled in the study until the result of the corrected plasma calcium level is known. Only those patients that do not have hypercalcaemia (corrected plasma calcium > 2.6 mmol/L) will be fully enrolled and randomised to receive vitamin D_3_ or placebo. Clinical data (including basic demographics, biochemical measures and CURB65 severity score) will be obtained from the patients’ hospital records and confirmed as needed by patient enquiry. A blood sample for 25OHD measurement will also be obtained at baseline.

